#### Stopping criteria

Receive blood transfusion, intervention, or surgery within 1 h after admissionPatients who died within 1 h after interventionPatients with serious adverse events or unexpected events in the clinical processPatients who did not complete the trial protocol observation period regardless of when or why they quitPatients ask to be withdrawn from the studyInvestigator termination of the study for any reason or any pathological event, adverse event, or change in the subject’s medical condition that leads the physician to conclude that continued participation in the study is not in the best interest of the patient

#### Termination study conditions

If a serious adverse event (SAE) occurs in the trial, the trial should be terminated in timeIf a major error in the clinical trial scheme is found in the trial, or there is a serious deviation in the scheme’s implementation. It is difficult to evaluate the efficacy of the drug. The trial should be suspendedIn the trial, it was found that the drug treatment effect was not effective (there was no therapeutic effect compared with the control group, the difference of each observation index was not statistically significant), it did not have clinical value, and the trial should be suspendedThe sponsor is asked to stop the trial

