### Secondary endpoints

(A)The amount of drug use, the total amount of resuscitation fluid, and the use of vasoactive drugs was compared in each study arm.(B)The total number of deaths and mortality was compared. The Kaplan–Meier survival curve was drawn, and the 7-day mortality of patients in each study arm was compared.(C)The levels of inflammatory mediators (PLA2, TNF- α, IL-6, PCT, CRP) were compared in each study arm.(D)The recurrence rate of shock and the complications of survival cases (ARDS, AKI, TIC, MODS, etc.) were compared among the study arms.(E)Blood coagulation and platelet function (PT, APTT, TT, INR, ACT, Fib, VEM) were compared among different study arms and before and after treatment.(F)Body temperature and acidosis (T, PH, BE, Lac, PaCO_2_, HCO_3_^−^) was compared among different study arms and before and after treatment.(G)The mechanical ventilation time, EICU hospitalization time, and total hospitalization time of patients in each study arm was compared.

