#### Pharmacovigilance plan

An adverse event (AE) is defined as any adverse medical event that occurs to a patient, which does not necessarily have a causal relationship with the treatment. Therefore, an adverse event can be any discomfort or unconscious signs (including abnormal laboratory results), symptoms, or disease after using the drug, whether or not it is considered drug-related. Such incidents can occur when used by the drug instructions or due to accidental or intentional overuse, drug abuse, or drug withdrawal. Any pre-existing condition or deterioration of the disease is also considered to be adverse. If it meets any of the following criteria, it will be considered a serious adverse event (SAE): the subjects died, endanger one’s life, extended hospital stay / ICU time, persistent or apparent disability/loss of function, an important medical event that requires medication or surgery to avoid serious consequences. In the event of a serious adverse event, whether or not the incident is related to the research drug or reference substance (if applicable), the doctor should notify the Research Supervision team within 24 h of the incident. The specimen management system for patients with adverse events will actively treat the patients and terminate the trial in the event of adverse events, and the remaining drugs will be uniformly recovered and centrally destroyed. The patient’s blood, body fluids, secretions, and other test-related specimens will be destroyed and recorded under the supervision of the main person in charge and the inspectorate.

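### The trial-level stop rule ends the trial at any SAE, yet death is defined as an SAE and 7-day mortality is an endpoint

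*Protocol article*

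**What the plan says.** Four places in the protocol article bear on what happens after a serious event.

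- **Termination study conditions.** "If a serious adverse event (SAE) occurs in the trial, the trial should be terminated". The item carries no condition on relatedness, number of events or prior review. The other items in the list (a major error in the scheme or its conduct, lack of effect, a sponsor request) all concern the trial as a whole.
- **Stopping criteria.** This separate list is about individual patients. It includes those "with serious adverse events or unexpected events in the clinical" process and those "who died within 1 h after" the intervention. A further item covers an adverse event or change in "medical condition that leads the physician to conclude that continued participation in the study is not in the best interest of the patient".
- **Pharmacovigilance plan.** The definition of seriousness begins: "it will be considered a serious adverse event (SAE): the subjects died". It goes on to threat to life and to longer hospital or ICU stay, among other criteria. For any SAE, related or not, "the doctor should notify the Research Supervision team within 24 h of the incident". A later sentence, hard to parse, says that the system for managing specimens of patients with adverse events "will actively treat the patients and terminate the trial in the event of adverse events".
- **Secondary endpoints.** Total deaths are compared, a Kaplan–Meier curve is planned, and "the 7-day mortality of patients in each study arm was compared". Shock recurrence and complications (ARDS, AKI, TIC, MODS) are also compared.

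**The concern.** The events that trigger termination of the whole trial include events that the trial sets out to count. Death is an SAE by the article's own definition and is also a secondary endpoint. Many cases of ARDS, AKI or MODS would meet the SAE definition too, through threat to life or a longer ICU stay. In a population that the abstract describes as having high mortality, a rule that ends the trial at one such event cannot be carried out together with a 400-patient comparison of 7-day mortality.

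If the rule is followed, the trial ends very early for a reason unrelated to the relative safety of the two fluids. If it is quietly ignored, the protocol has no workable written rule for when SAEs should end the trial, and the investigator must guess whether the Pharmacovigilance sentence refers to the patient or to the trial.

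**Working it through.** **Step 1: set the sections side by side.**

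| Section | Trigger | What stops |
|---|---|---|
| Termination study conditions | an SAE, unqualified | the trial |
| Stopping criteria | an SAE or unexpected event; or an adverse event on the physician's judgement | the patient |
| Pharmacovigilance plan | adverse events, not limited to serious ones | unclear: patient or trial |
| Secondary endpoints | deaths and complications | nothing; they are counted to day 7 |

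The clash is between the first row and the last, given that the Pharmacovigilance plan makes death an SAE. The Stopping criteria add evidence: by listing death within 1 h as a reason to stop a patient, they presume that the trial goes on after a death.

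**Step 2: how soon would the rule act?** The article gives no figure for this, so there is none to reproduce. The inputs are:

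- Planned size: 400 patients (Sample size section).
- 7-day mortality p: not given. Assumed range 2% to 30%.
- Patients treated as independent, and deaths alone counted. Other SAEs would only bring the stop forward.

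Formulas:

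- Expected position of the first patient to die = 1/p.
- Smallest n with at least a 95% chance of one or more deaths: 1 − (1 − p)^n ≥ 0.95, so n = ln(0.05)/ln(1 − p), rounded up.
- Chance of no death in 400 = (1 − p)^400.

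Worked at p = 2%: 1/0.02 = 50; ln(0.05)/ln(0.98) = 148.3, so 149; 0.98^400 = 0.0003.

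| Assumed p | Expected position of first death | 95% likely by patient | Chance of none in 400 |
|---|---|---|---|
| 2% | 50 | 149 | 0.0003 |
| 5% | 20 | 59 | 1.2 × 10⁻⁹ |
| 10% | 10 | 29 | 5.0 × 10⁻¹⁹ |
| 30% | 3.3 | 9 | 1.1 × 10⁻⁶² |

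As a stress test below the range, p = 1% gives 0.99^400 = 0.018, so the full 400 would still be reached without a death less than 2% of the time.

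**Step 3: what this does to the endpoint.** A completed trial would expect 400 × 0.02 = 8 to 400 × 0.30 = 120 deaths for the mortality comparison. Under the written rule it would have one, or a few if further patients were already enrolled when the first death occurred. No comparison between arms can rest on that.

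**The case against.** The best defence is that this is loose drafting and not an operating rule. The article uses the language of termination for single patients elsewhere: the last Stopping criterion speaks of the investigator ending the study when it plainly means one patient's participation. The Pharmacovigilance sentence concerns patients with adverse events and can be read the same way. The Exclusion criteria, Stopping criteria and Secondary endpoints all presume that deaths occur while the trial runs. The Trial status section reports recruitment from May 2021, a version 5.0 dated September 2022, and an expected end in June 2024. The mortality range is also assumed, and that a death will occur among 400 shock patients hardly needs a calculation.

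Much of this stands. It makes it likely that nobody intends to apply the rule literally. It does not repair the rule, which sits in the trial-level list, apart from the patient-level one, beside items that can only concern the whole trial.

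Two stronger readings are tempting and should not be drawn.

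- **That the stop rules cannot all be followed.** Stopping the patient and then stopping the trial are compatible actions, so the Stopping criteria do not by themselves exclude the trial-level rule. The conflict lies with the endpoints and the SAE definition.
- **That patients stopped for an SAE leave follow-up, so that last observation carried forward biases the 6 h lactate endpoint.** The SAE item does not say that measurement ends. The wording about continued participation belongs to the separate physician-judgement item. The Schedule of intervention follows enrolled patients for 7 days without exception. No SAE rate is given, so neither the size nor the direction of any bias can be derived.

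**Conclusion.** The point holds for the trial-level rule. As written, an unqualified SAE condition would end the trial at its first death or other SAE. That cannot be reconciled with comparing deaths, 7-day mortality and serious complications in 400 patients. The conflict itself follows from the text alone. Its speed depends on an assumed 7-day mortality of 2% to 30% and on independence between patients, but the conclusion is insensitive to the rate within that range.

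The ambiguity in the Pharmacovigilance plan is a lesser, related defect: its sentence does not settle whether the patient or the trial is terminated.

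This is a wrongly stated rule, not a detail left to a fuller document. It should be corrected. It does not show that the trial has been or will be stopped this way, and it does not show that the primary analysis is invalid.

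**What to change.** 1. **Termination study conditions.** Replace automatic termination on any SAE with prompt safety review of SAEs, and end the trial only on the outcome of that review. The 24 h notification to the Research Supervision team already supplies the reporting route.
2. **Stopping criteria and Pharmacovigilance plan.** State that an SAE, or an adverse event that the physician judges to warrant it, stops study fluid for that patient only. State that scheduled follow-up to day 7 continues unless consent is withdrawn. This settles what is meant by terminating the trial on adverse events.

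**Cost.** No new visits or samples are needed, because assessments to day 7 are already scheduled. Recruitment is under way, however, and the section on communicating amendments requires regulatory approval before an important change takes effect, so this needs a formal protocol amendment.

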## Methods

### Study design

This study is a clinical single-center, prospective, superiority, parallel-group, randomized controlled trial in patients with THS. The study will be conducted at the Department of Treatment Center for Traumatic Injuries and Emergency Intensive Care Unit (EICU) of the Third Affiliated Hospital of Southern Medical University, China. Patients who meet the eligibility criteria and obtain informed consent will be assigned to the test group or control group in a 1:1 ratio based on the size of the random number allocated to them. Patients will be resuscitated with the drug according to the study arm, and only this drug will be used for resuscitation in the early fluid resuscitation (6 h) period. Approval has been obtained from the Institutional Ethics Committee (IEC) of the Chinese Ethics Committee of Registering Clinical Trials. This study complies with the Declaration of Helsinki and the relevant regulations for clinical research in China. This trial has been registered as ChiCTR2100045044.

The protocol is written in accordance with the Standard Protocol Items: Recommendations for Interventional Trials (SPIRIT) guidelines, shown in Additional file 2. Figure 1 (study scheme) shows an overview of the study process. Figure 2 shows the schedule of enrolment, interventions, and assessments.

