#### Blinding

This trial is an open-blinding trial, because patients are usually unconscious and the packaging of the two trial drugs (BRS and LRS) differs significantly.

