#### Data and safety monitoring

Investigators need to fill in the data collected in the case report form (CRF) according to the requirements of the research program. At the end of the study, the investigator will submit the case reports of all patients selected for this study to the data management center, which should be complete and signed. The consistency of the collected case reports table data will be checked. The inconsistent data will be questioned, and the responsible doctor will be required to clarify. Before starting the trial, unified training will be given to the investigator to clarify the purpose of the study and ensure that the same test methods are used in the trial. The investigator must research in strict accordance with the requirements of the research program. Patients are randomly and distributed by statisticians and data management centers, and the doctor is responsible for in putting information into the case report form. The CRF supervisor will check the completeness and accuracy of the CRF and guide the research center staff to make necessary modifications or supplements. The CRF is sent to the data processing by the regional supervisor, one copy is retained in the research center, and the other one is used as an attachment to the supervisor’s work. CRF will hand it over to a reliable medical data processor for data entry. Data items in CRF will be entered into the research database using a multiple-input method with secondary input audits. Text items (such as comments) can only be checked manually after entering once from CRF. The data manager then systematically checks the information entered into the database using error messages printed from the confirmer program and the database list. The database will be locked after it is declared complete and correct. After that, any changes to the database can only be achieved with the written consent of clinical research leaders, research statisticians, and data managers.

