#### Sample size

The trial design of this study was a positive drug, parallel-group, and superiority verification. The primary endpoint is the duration of shock and lactic acid clearance rate during the early fluid resuscitation period (6 h). Both primary endpoints were required to be met simultaneously, and Bonferroni correction was used as appropriate. The alpha value = 0.025 (one-sided), power = 0.80 were set. The total sample size was finally determined to be 400 cases with 200 cases in each study arm.

The calculations were as follows:Lactic acid clearance rate: According to a study by Wang et al., the mean value of lactic acid clearance rate after 6 h of fluid resuscitation in the control group was 32% with a standard deviation of 10%, and the expected lactic acid clearance rate after 6 h of fluid resuscitation in the test group was 35% with an equal standard deviation for both study arms [42]. The calculated sample size was 176 cases for each study arm, and a total of 392 cases were required based on 10% of the loss to follow-up.Duration of shock: According to the pre-experimental study, the duration of shock in the control group was 3 h, and in the test group the duration of shock was 1.5 h, with a standard deviation of 4 h. Assuming equal standard deviation for both study arms, the sample size calculated for both study arms was 113 cases, and a total of 252 cases were required based on 10% of the loss to follow-up.

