#### Interim analyses

No interim analysis will be performed.

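### The rule that suspends the trial for non-significant differences needs a between-arm comparison during the trial, which the protocol's own statement on interim analyses excludes

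*Protocol article*

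**What the plan says.** The protocol article describes a "clinical single-center, prospective, superiority, parallel-group, randomized controlled trial" with 200 patients per arm.

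- **Termination study conditions.** The third condition applies when the drug is found, during the trial, not to be effective. In parentheses this is explained as "there was no therapeutic effect compared with the control group, the difference of each observation index was not statistically significant". The sentence adds that the drug lacks clinical value and ends with suspension of the trial.
- **Interim analyses.** The whole section reads "No interim analysis will be performed".
- **Data and safety monitoring.** "At the end of the study, the investigator will submit the case reports of all patients selected for this study to the data management center".
- **Blinding.** "This trial is an open-blinding trial".
- **Sample size.** "The alpha value = 0.025 (one-sided), power = 0.80 were set". On the two primary endpoints, shock duration and 6-hour lactate clearance: "Both primary endpoints were required to be met simultaneously, and Bonferroni correction was used as appropriate".

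**The concern.** A condition for suspending a trial has meaning only while the trial is running. This one depends on whether differences between the arms are statistically significant, so someone must compare efficacy outcomes by arm before the end. That is an interim analysis, whatever it is called, and the protocol says there will be none. Staff cannot follow both statements: either the condition can never be applied, or the statement on interim analyses is untrue.

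The content of the condition is a second problem. A superiority trial is given 200 patients per arm because fewer would often miss the assumed effect. Halfway through recruitment, a non-significant difference is an ordinary result for a treatment that works as planned, so it is a poor sign of futility. If the condition were acted on, a trial of an effective fluid could be halted before it can answer its question.

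**Working it through.** **Inputs (Sample size section).** Lactate clearance 35% against 32%, SD 10 points, so d = 3/10 = 0.30. Shock duration 1.5 h against 3 h, SD 4 h, so d = 1.5/4 = 0.375. One-sided alpha 0.025, power 0.80, loss to follow-up 10%.

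**Step 1: reproduce the plan's figures.** For a two-sample t-test with n per arm, the noncentrality is d·√(n/2) with 2n − 2 degrees of freedom.

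- Lactate clearance, n = 176: 0.30·√88 = 2.81, critical t = 1.967, power 0.801.
- Shock duration, n = 113: 0.375·√56.5 = 2.82, critical t = 1.971, power 0.801.
- With loss to follow-up: 176/0.9 = 195.6, rounded up to 196 per arm, 392 in total. 113/0.9 = 125.6, rounded up to 126 per arm, 252 in total.

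All four stated figures reproduce, so the same model can be used at smaller n.

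**Step 2: power at partial recruitment, assumed effects true.** The article gives no look times. The values of n are assumptions and count evaluable patients.

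| n per arm | Noncentrality (lactate, shock) | Power, lactate | Power, shock duration |
|---|---|---|---|
| 50 | 1.50, 1.88 | 0.318 | 0.459 |
| 100 | 2.12, 2.65 | 0.560 | 0.751 |

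**Step 3: chance that both primary endpoints are non-significant.** The correlation between the endpoints is not given, so two extremes are shown.

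- Independent: (1 − power₁)(1 − power₂). At 50 per arm, 0.682 × 0.541 = 0.37. At 100 per arm, 0.440 × 0.249 = 0.11.
- Perfectly correlated: 1 − the larger power. At 50 per arm, 1 − 0.459 = 0.54. At 100 per arm, 1 − 0.751 = 0.25.

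The ranges are therefore 37-54% and 11-25%.

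**Step 4: cost in power.** A simulation of 1,000,000 trials used 180 evaluable patients per arm (200 less 10%), endpoint correlation from 0 to 0.8, and one look at half the patients (90 per arm). Stopping when both primaries were non-significant ended 14-26% of trials. Power to meet both primaries fell from 77-80% to 66-69%.

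**Step 5: the literal wording.** Read strictly, every observation index must be non-significant, not only the two primaries. As an illustration, assume 20 further independent indices on which the fluid has no effect. All 20 are non-significant with probability 0.95²⁰ = 0.36. The independent figures then fall to 0.37 × 0.36 = 0.13 at 50 per arm and 0.11 × 0.36 = 0.04 at 100. Correlation among the indices would weaken this reduction. True effects on them would strengthen it.

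**The case against.** The strongest reply is that this is a drafting conflict in a generic list, not a working stopping rule. The plan excludes interim analysis, and case reports reach the data management center only at the end, so no described route would trigger the condition. The trigger is also narrower than non-significance alone: it covers each observation index, it mentions absence of clinical value as well, and the action is suspension, although it stands under a termination heading. All of this stands. It limits what can be said about consequences, but it does not reconcile the two sections.

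The absence of look times, a minimum number of patients or a futility boundary is no fault in itself. The article condenses a fuller protocol, which may hold such details. However, further detail about looks could not be squared with a statement that there are none.

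A reader might infer three stronger claims that the documents do not support:

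- **An effective fluid would probably be stopped.** The percentages cover only the two primaries at assumed looks. The literal condition triggers less often, and nothing shows that looks will be taken.
- **The type I error is inflated.** Stopping only for non-significance does not by itself raise the one-sided error.
- **The rule causes biased enrolment or biased judgement of when shock ends.** That risk comes from open-label conduct, in which the investigators already know each patient's arm. No section ties it to this condition.

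**Conclusion.** The contradiction is certain from the text: a suspension condition that turns on significance between arms cannot coexist with a plan for no interim analysis. The condition is also badly chosen, because in a partly recruited superiority trial non-significance says little about futility.

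Its size can be given only conditionally. If the two primaries alone were tested, with the assumed effects true, a single look would find both non-significant in 37-54% of trials at 50 per arm and in 11-25% at 100 per arm. This rests on the protocol's effect sizes and SDs, t-tests at one-sided 0.025, assumed looks, and endpoint correlation anywhere from none to perfect. Requiring every secondary index to be non-significant as well would lower these figures by an amount the documents do not determine. The point must be corrected, because the condition is wrong as written and not merely short of detail.

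**What to change.** Delete the non-significance condition from Termination study conditions. Keep the Interim analyses section as it is, and add one sentence there stating that no between-arm comparison of efficacy is made before database lock.

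The cost is one short protocol amendment. The small downside is that an ineffective fluid cannot be dropped early, which the absence of interim analyses already implies. If the sponsor does want futility stopping, the alternative is a prespecified non-binding futility analysis at a fixed information fraction, reviewed by an independent committee, with the Interim analyses section rewritten to match. That is a larger change.

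The other conditions in the termination list are a separate matter, and this fix leaves them unchanged.
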